## Study Design and Procedures

This randomized, prospective, 2-arm, parallel-group, double-blind, placebo-controlled superiority trial will evaluate the efficacy of montelukast in decreasing disease severity of dengue patients. The primary objective is to determine whether montelukast is more effective than placebo in reducing dengue with warning signs. Other important study objectives are to access the efficacy of montelukast in decreasing hemoconcentration, thrombocytopenia, hospitalization, length of hospital stay, severe dengue, dengue shock, and mortality.

The study cohort will include 358 patients aged 20 years or above with positive NS1 antigen test. Participants will be recruited over a 2-year period at 2 hospitals and will be followed up for up to 14 days.

The objectives are as follows:

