### **Randomization and allocation concealment**

Eligible patients will be randomized using a computer-generated randomisation list prepared by an independent statistician and stratified by the centre with a block size of four in a 1:1 ratio to one of the two treatment arms:

Arm 1: montelukast 10 mg

Arm 2: placebo 10 mg

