### Outcomes

The **primary objective** is to provide reliable estimates of the effect of montelukast on the incidence of dengue warning signs, which will be assessed during the defined period, 14 days or until the discontinuation of the follow up appointment by the attending physicians, whichever is shorter. Those who missed the follow-up appointment will be recorded as missing values after the time of the last known status.

The **secondary objectives** are to assess the effects of montelukast on components of composite outcomes of dengue with warning signs, hospitalization, length of hospital stay, severe dengue, dengue shock, and mortality.

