### Methods of analysis

Comparisons will be made between all participants randomized to the different treatment arms, irrespective of whether they received their allocated treatment (“intention-to-treat” analyses).

The primary analysis will apply Cox proportional hazards regression to all randomized participants to compare the time from randomization to the first occurrence of dengue with warning signs between the two treatment groups. The model will include an indicator for intervention arm as its sole predictor variable. Clinical site at randomization will be a stratifying factor. Follow-up time will be censored at the last date of event ascertainment. The p-value from the primary analysis will be based on the chisquare statistic from a likelihood ratio test obtained from proportional hazards models with and without the term for intervention arm. This likelihood ratio test will constitute the primary test of statistical significance for the primary analysis. Tests of heterogeneity or trend will generally be used to assess disparity in efficacy among different subgroups (e.g. men vs. women; age group, high vs. low viral load, dengue serotypes). One sided tests at the 0.025 level are used.

The secondary analysis will be analyzed using chi-square test or Fisher exact test for categorical variables, and Student T-test or Wilcoxon rank-sum test for continuous variables. These will be reported with 95% confidence intervals and nominal p-values.

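### Secondary outcomes are tested without a centre term although randomization and the primary model are stratified by centre: a small, conservative loss of precision that one sentence would remove

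*Protocol*

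**What the plan says.** Under Randomization and allocation concealment, the protocol says that allocation is "stratified by the centre with a block size of four in a 1:1 ratio to one of the two treatment arms". Study Design and Procedures gives the number of centres: "Participants will be recruited over a 2-year period at 2 hospitals".

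Methods of analysis carries the stratification into the primary Cox model: "Clinical site at randomization will be a stratifying factor". The next paragraph turns to the secondary outcomes and names other methods: "The secondary analysis will be analyzed using chi-square test or Fisher exact test for categorical variables". Outcomes on a continuous scale get a choice of two further tests: "Student T-test or Wilcoxon rank-sum test for continuous variables". It mentions no centre term, and adds: "These will be reported with 95% confidence intervals and nominal p-values".

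The Outcomes section lists what these tests apply to: "components of composite outcomes of dengue with warning signs, hospitalization, length of hospital stay, severe dengue, dengue shock, and mortality".

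**The concern.** Blocks of four within each hospital keep the arms almost equal in size within each hospital. A difference between the hospitals therefore contributes almost nothing to the difference between the arms, whose sampling variance is close to the within-centre variance. A two-sample test that ignores centre estimates its standard error from the total variance, which also contains the between-centre part. When the hospitals differ, that standard error is too large.

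The outcomes most exposed are hospitalization and length of stay, because both depend partly on local clinical decisions. The protocol also lets the attending physicians decide when follow-up appointments stop (Collecting follow-up information; Duration of follow-up), so local practice could affect what is observed. What is at stake is precision in outcomes that, under Secondary Hypotheses, are meant to back up the primary result.

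**Working it through.** **Inputs from the protocol.** Two centres, 1:1 allocation in blocks of four within centre, N = 358; chi-square or Fisher, and t-test or rank-sum, for the secondary outcomes. The protocol gives no centre-specific rates, means or recruitment shares, so those below are assumptions.

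**The protocol's own figure.** The only stated power figure concerns the primary endpoint. With 54.5% against 39.5%, one-sided 2.5% and 80% power, the unpooled formula gives (1.96 + 0.8416)² × (0.545×0.455 + 0.395×0.605) / 0.15² = 169.87, so 170 per arm and 340 in total. Allowing for 5% loss, 340/0.95 = 357.9, or 358. The stated sample size reproduces and is not in question. No power is claimed for any secondary outcome.

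**Binary outcomes.** Let a share w of patients come from centre 1, with rates p₁ and p₂ and overall rate p̄.

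- Total variance: p̄(1 − p̄)
- Within-centre variance: w·p₁(1 − p₁) + (1 − w)·p₂(1 − p₂)
- R = within-centre / total; standard-error inflation = 1/√R
- True size of a nominal two-sided 5% test: 2[1 − Φ(1.96/√R)]
- Power where the stratified test has 80%: Φ(2.80 − 1.96/√R)

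Equal centres (w = 0.5):

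| Assumed rates | Within / total | R | SE inflation | True size | Power |
|---|---|---|---|---|---|
| 40% / 60% | 0.24 / 0.25 | 0.96 | 2.1% | 4.5% | 79% |
| 30% / 70% | 0.21 / 0.25 | 0.84 | 9.1% | 3.2% | 75% |
| 10% / 30% | 0.15 / 0.16 | 0.94 | 3.3% | 4.3% | 78% |
| 2% / 8% | 0.0466 / 0.0475 | 0.98 | 1.0% | 4.8% | 79% |

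**Unequal centres.** With an 80:20 split, power becomes 79.3% at 40%/60% and 76.6% at 30%/70%. With a 90:10 split it is 79.6% and 78.1%. For rates around 50% the loss shrinks as the centres become unequal. At low rates this need not hold for a moderate split: at 10%/30% a 70:30 split leaves the inflation at 3.3%, and at 2%/8% it is 1.1% instead of 1.0%. Both remain small.

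**Simulation.** N = 358, near-equal centres balanced between arms, a 15-point effect, 200,000 runs:

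| Control rates by centre | Size, no centre term | Size, CMH | Power, no centre term | Power, CMH |
|---|---|---|---|---|
| 49.5% / 59.5% | 4.9% | 4.9% | 81.7% | 81.7% |
| 44.5% / 64.5% | 4.5% | 4.9% | 81.9% | 82.6% |
| 34.5% / 74.5% | 3.2% | 4.9% | 83.6% | 87.7% |

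The simulation confirms the direction and order of size: under one point of power at a 20-point gap, about four points at a 40-point gap.

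**Continuous outcomes.** With equal centres whose means differ by d within-centre SDs, the t-test standard error is inflated by √(1 + d²/4).

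- d = 0.2: √1.01 = 1.005 (0.5%)
- d = 0.5: √1.0625 = 1.031 (3.1%; power 78% instead of 80%)
- d = 1.0: √1.25 = 1.118 (11.8%; power 73%)

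The rank-sum and Fisher tests were not quantified. The same reasoning gives the direction.

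**The case against.** The strongest reply is that little is lost. The protocol has nothing to show that the two hospitals differ, and both enrol the same kind of patient: adults with confirmed dengue and no warning signs. At a gap of 20 points, already sizeable, the cost is about one point of power. Severe dengue, shock and death may well be rare in such patients, and there centre hardly matters. The secondary p-values are labelled nominal and no power is promised for them, so no stated claim fails. All of this stands, and it sets the priority low.

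A second reply is that the methods paragraph is only an outline, never excludes site adjustment, and leaves detail to a statistical analysis plan that is not shown. This stands only in part. The protocol is not silent: it names procedures. The t-test, the Fisher exact test and the rank-sum test are two-sample procedures without strata; only the term chi-square could loosely cover a stratified version. An analysis plan with stratified methods would depart from this text.

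Three stronger readings are tempting and unsupported.

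- A reader might infer that the secondary tests are invalid or prone to false positives. The error runs the other way: true size falls below 5%.
- A reader might infer a heavy loss of power. A fall to 64% needs equal centres with rates of 20% and 80% (R = 0.16/0.25 = 0.64), and nothing in the protocol points to a 60-point gap.
- A reader might infer that the two methods paragraphs contradict each other. The site-stratification sentence belongs to the primary model only, so this is a difference in treatment between the analyses.

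**Conclusion.** The point holds as a minor matter of efficiency and consistency. The protocol stratifies the randomization and the primary model by centre, then fixes secondary tests that ignore centre. If the hospitals differ, the secondary intervals are somewhat too wide and the p-values somewhat too large. Type I error and the primary result are not at risk.

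The mechanism and its direction follow from the design; the size is assumed. For gaps up to 20 points the standard-error excess is about 0.5% to 3%. It becomes material only if the hospitals differ greatly: about 9% at a 40-point gap, or about 12% for a one-SD difference in a continuous outcome, with equal centres. For rare outcomes it is negligible.

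**What to change.** Amend the sentence on secondary outcomes in Methods of analysis:

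- **Categorical outcomes:** Cochran-Mantel-Haenszel tests and risk differences stratified by centre, with exact stratified methods where events are sparse.
- **Continuous outcomes:** the van Elteren (centre-stratified rank-sum) test, or a linear model with centre as a term.

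Any statistical analysis plan should say the same. Specify the change before unblinding, so that it cannot be seen as a choice made after looking at the results. It costs a change of wording and uses standard software; the sample size of 358 and the data collection stay as they are.

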### Data and safety monitoring board

An independent Data and Safety Monitoring Board will be established to monitor data and oversee participant safety. Members will be appointed by the Research Unit, Phramongkutklao Hospital to provide oversight of the trial. Meetings of the DSMB will be held at least every 12 months. Material for these meetings will be distributed two weeks in advance of the meetings. Up-to-date statistical analyses will be provided to the DSMB in preparation for their meetings. The analyses will include data on recruitment, outcome measures, any side-effects or safety concerns, and will be designed in cooperation with the DSMB. Interim analyses of the intervention effectiveness will be performed at times coinciding with the meetings of the DSMB, and will be controlled to protect the overall Type

I error of the trial. The planned interim analysis is at 50% and 75% of the enrollment, with alpha spending by Lan-DeMets spending function with O'Brien-Fleming type boundaries ( $\alpha=0.006$ ,  $\alpha=0.018$ , and  $\alpha=0.026$ , respectively)

These results will be for the use of the DSMB and will not be revealed to the investigators. The purpose of these analyses will be for the DSMB to assess the trial progress with respect to intervention efficacy and safety, for possible recommendations regarding early termination of the trial.

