## Statistical Analysis

### Sample size and power

Based on findings in a study reporting the incidence of dengue with warning signs excluding lethargy, (21) we have assumed a 54.5% event rate of the primary outcome in the standard group. Regarding the 22% absolute risk reduction in dengue shock syndrome in an open-label study, (20) we have assumed a 15% effect size for the intervention (absolute risk reduction of 0.15). With a 5% rate of loss to follow-up, and a one sided test at the 2.5% level, a sample size of 358 provides approximately 80% power to detect a reduction in the primary endpoint between the two arms.

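### The three interim and final alphas are increments of a total of 0.05, while the protocol declares a one-sided 0.025 test and does not say on what scale the alphas apply

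*Protocol*

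**What the plan says.** The protocol fixes the test level in two places. Under Sample size and power it uses "a one sided test at the 2.5% level". Under Methods of analysis it says "One sided tests at the 0.025 level are used", and it takes the primary p-value from a likelihood-ratio chi-square for the treatment term in a Cox model.

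Under Data and safety monitoring board it promises that the interim analyses will protect the overall type I error. It plans looks at 50% and 75% of enrolment, "with alpha spending by Lan-DeMets spending function with O'Brien-Fleming type boundaries", and prints three alphas in order for the two interims and the final analysis: 0.006, 0.018 and 0.026. It does not say whether these are amounts of alpha spent at each look, cumulative spend or nominal p-value thresholds. It does not say whether they are one- or two-sided.

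**The concern.** The printed alphas are the rule by which the board could recommend stopping for efficacy and by which the final result is declared. A board statistician will most naturally compare a p-value with them. They do not correspond to the declared one-sided 0.025, and what they deliver depends on a choice that the protocol leaves open. On some readings the trial has a higher false-positive rate than it declares. On another it gives up several points of power for nothing. Two people who follow the same text could reach different decisions on the same data.

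**Working it through.** **Inputs.** Declared level: one-sided 0.025. Looks: 50%, 75% and 100% of enrolment. Printed alphas: 0.006, 0.018, 0.026. Assumption: the information fractions t equal the enrolment fractions, 0.5, 0.75 and 1. In a Cox analysis information follows events, so the actual fractions may differ somewhat.

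**Step 1: where the printed figures come from.** The O'Brien-Fleming type spending function is a(t) = 2 − 2Φ(z₁₋α/₂ / √t).

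| Total alpha | Cumulative spend at 0.5, 0.75, 1 | Increments |
|---|---|---|
| 0.05 (z = 1.960) | 0.0056, 0.0236, 0.0500 | 0.0056, 0.0181, 0.0264 |
| 0.025 (z = 2.241) | 0.0015, 0.0096, 0.0250 | 0.0015, 0.0081, 0.0154 |

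The first row rounds to 0.006, 0.018 and 0.026. The second row does not match. So the printed figures are increments for a total of 0.05, and 0.006 + 0.018 + 0.026 = 0.050.

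**Step 2: what the figures deliver on each reading.** The error is the probability of crossing the benefit boundary at any look under no effect. It is found by numerical integration over the joint normal statistics, with correlation √(tᵢ/tⱼ) between looks.

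| Reading | z at the three looks | One-sided error |
|---|---|---|
| One-sided increments | 2.512, 2.012, 1.723 | 0.050 |
| One-sided p-value cut-offs | 2.512, 2.097, 1.943 | 0.035 |
| Two-sided p-value cut-offs | 2.748, 2.366, 2.226 | 0.018 |
| Two-sided increments, symmetric bounds | 2.748, 2.295, 2.046 | 0.025 |

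Read as cumulative spend, the figures end at 0.026 rather than 0.025 and do not follow the 0.0015, 0.0096, 0.0250 curve.

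The fourth reading reaches the declared level, but the two-sided p-value cut-offs that it implies are about 0.006, 0.022 and 0.041. The last two are not the printed figures.

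**Step 3: the boundary for one-sided 0.025.** Solving for the z-values that spend 0.0015, 0.0096 and 0.0250 cumulatively gives z = 2.963, 2.359 and 2.014. The nominal one-sided p-values are 0.0015, 0.0092 and 0.0220, and the two-sided equivalents are 0.0031, 0.0183 and 0.0440.

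**Step 4: power.** The protocol's own figure first. From "we have assumed a 54.5% event rate of the primary outcome in the standard group" and "absolute risk reduction of 0.15", the rates are 0.545 and 0.395. One-sided 0.025 and 80% power need 173 per arm, or 346 in total. With 5% loss, 346 / 0.95 = 365 (rounded up), against 358 stated. With 358 × 0.95 / 2 = 170 evaluable per arm, power is 79.4%, which agrees with the stated 80% or so.

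Take a fixed design with exactly 80% power, so that the expected final z is 1.960 + 0.842 = 2.80. Power is then:
- 79.2% with the one-sided 0.025 boundary of step 3;
- 78.7% with two-sided increments;
- 73.7% with the printed figures used as two-sided p-value cut-offs.

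**The case against.** The strongest objection is that a coherent reading exists. The text speaks of alpha spending, so the figures may well be increments. A likelihood-ratio chi-square p-value is naturally two-sided. Two-sided increments totalling 0.05 with symmetric bounds leave 0.025 in the benefit tail, which is the declared level, and power is within half a point of the boundary in step 3. This stands. It rules out the inference, which a reader might draw from the sum alone, that the rule fails however it is read. But this reading is not stated, it sits beside two declarations of one-sided testing, and it needs cut-offs that appear nowhere in the protocol.

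Three other inferences are also too strong:

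- **That the overall error is simply twice the declared level.** Adding the alphas gives the error only if they are one-sided increments. As one-sided cut-offs the error is 0.035, because the looks are correlated. As two-sided cut-offs the rule is conservative.
- **That 0.026 at the end exceeds the whole 0.025 budget, or that 0.006 at the first look is about four times too lenient against 0.0015.** Both treat the figures as one-sided cut-offs. An increment is not a threshold, and on the two-sided scale the first-look comparison is 0.006 against 0.0031, about twice.
- **That the board's meeting schedule contradicts the planned looks.** The protocol says "Interim analyses of the intervention effectiveness will be performed at times coinciding with the meetings of the DSMB". But 12 months is the longest allowed interval between meetings, so meetings can be set at 50% and 75%. Those two looks are named as the planned interim analyses, and the spending approach can accommodate other look times. No contradiction is shown.

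**Conclusion.** The concern holds in this form: the printed alphas belong to a total of 0.05, the declared test is one-sided 0.025, and the protocol gives neither scale nor sidedness to connect the two. Used directly as p-value cut-offs, the figures miss the declared level in either direction: 0.035 with one-sided p-values, or 0.018 with two-sided p-values and about 74% power instead of 80%. As one-sided increments they give 0.050. The two-sided increment reading would deliver 0.025, so this is a decision rule that is wrong or unusable as printed, not proof that the trial must overspend.

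The sizes rest on information fractions of 0.5, 0.75 and 1. The origin of the figures is clear: all three match the increments for a total of 0.05 to the digits printed. The rule governs early stopping and the primary claim, so it should be corrected before any unblinded efficacy look.

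**What to change.** Replace the three figures by the Lan-DeMets O'Brien-Fleming type nominal one-sided levels 0.0015, 0.0092 and 0.0220 (z = 2.963, 2.359, 2.014), with a total one-sided alpha of 0.025. Label them as nominal p-value thresholds. Because the primary p-value comes from a chi-square, add the two-sided equivalents 0.0031, 0.0183 and 0.0440, to be met with the effect in favour of montelukast. State that the values are provisional and are recomputed at each look from the observed fraction of primary events. Restate power as about 79%.

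If the sponsor did mean two-sided increments, saying so and printing the matching z-bounds (2.748, 2.295, 2.046) would also reconcile the text. The one-sided replacement is simpler because it agrees with the level declared elsewhere.

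The cost is a sentence or two in the protocol, with the same wording carried into the board's charter if there is one. No extra patients are needed.

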## Ethical Aspects

### Ethical principles

This study will be conducted in accordance with the principles laid down by Thai Good Clinical Practice Guidelines and other Local Ethics Committees.

### Consent

The research coordinator will approach eligible patients as soon as their blood are positive for NS1 to obtain informed consent. Patients must be enrolled within 24 hours of positive NS1 antigen. Critically ill patients are excluded.

### Expected adverse events

Montelukast is well tolerated in in patients with asthma. (22) There were no significant differences between the montelukast and placebo treatment groups in the frequency of any adverse effect, with the exception of allergic rhinitis, which occurred more frequently in placebo than montelukast recipients.

In 2020, FDA required Boxed Warning about serious mental health side effects for montelukast, after 82 cases identified of completed suicide associated with montelukast, with many reporting the development of concomitant neuropsychiatric symptoms prior to the event. (23) Patients were suggested to stop taking montelukast and notify a health care professional if they experience behavior or mood-related changes while taking the medicine.

At each visit, the trial staff will specifically query participants for serious adverse events (SAEs). In addition, information on serious adverse events may also be reported to study staff spontaneously by participants through telephone calls. SAEs will be collected and reported from screening to the end of the study follow-up period for an individual participant. SAEs will be followed until resolution, stabilization, or until it is determined that study participation is not the cause. Reports of serious adverse events will be collected for review by the DSMB at their meetings.

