### **Administration of allocated treatment**

Study medication will be given 10 mg orally immediately and every day thereafter for 10 days or until recovery, defined as the discontinuation of the follow up appointment by the attending physicians, whichever is shorter.

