### **Collecting follow-up information**

The following information will be ascertained at least every other day for 14 days or until the discontinuation of the follow up appointment by the attending physicians, whichever is shorter.

- Clinical symptoms and signs of warning signs

- Hospitalisation status, death status
- Laboratory results

Follow-up information is to be collected on all study participants, irrespective of whether or not they complete the scheduled course of allocated study treatment. Study staff will seek follow-up information through various means including medical staff, reviewing information from medical notes, routine healthcare systems, and registries.

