#### **Duration of follow-up**

All randomised participants are to be followed up until the discontinuation of the follow up appointment by the attending physicians, whichever is shorter. It is recognised that in the setting of this trial, there may be some variability in exactly how many days post-randomisation information on disease status is collected. This is acceptable and will be taken account of in the analyses and interpretation of results, the principle being that some information about post-randomisation disease status is better than none.

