**Table 1: Trial procedure**

| Procedure                                      | D1 | D2-13 | D14 |
|------------------------------------------------|----|-------|-----|
| Informed consent                               | x  |       |     |
| Review of eligibility criteria                 | x  |       |     |
| Randomization                                  | x  |       |     |
| Demography, medical history, comorbidities     | x  |       |     |
| Physical examination                           | x  | x*    |     |
| Clinical evaluation                            | x  | x*    |     |
| Pregnancy test in women                        | x  |       |     |
| CBC                                            | x  | x*    |     |
| dengue RT-PCR                                  | x  |       |     |
| Side effects monitoring                        | x  | x*    | x   |
| Warning signs, severe dengue, and dengue shock |    | x*    | x   |
| Admission status                               |    | x*    | x   |

\*outpatients visit at least every other day, or daily inpatient visit until recovery

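### The protocol contradicts itself on when safety collection ends: the text ends it when the physician stops follow-up appointments, while Table 1 schedules a day 14 side-effects check for everyone

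*Protocol*

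**What the plan says.** Four parts of the Protocol's text bear on the end of safety collection, and Table 1 gives a fifth statement.

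- **Administration of allocated treatment.** Study medication is given "every day thereafter for 10 days or until recovery, defined as the discontinuation of the follow up appointment by the attending physicians, whichever is shorter", and this is the rule that ends dosing.
- **Collecting follow-up information.** Information is gathered "at least every other day for 14 days or until the discontinuation of the follow up appointment by the attending physicians, whichever is shorter". Study Design and Procedures gives the same cap: participants "will be followed up for up to 14 days".
- **Duration of follow-up.** The rule is restated here: "All randomised participants are to be followed up until the discontinuation of the follow up appointment by the attending physicians, whichever is shorter". No day limit appears in this version, so the closing comparison has only one alternative.
- **Expected adverse events.** "SAEs will be collected and reported from screening to the end of the study follow-up period for an individual participant". The same section cites the boxed warning on serious mental health effects of montelukast.
- **Table 1.** The row "Side effects monitoring" is marked at D1, at D2-13 with an asterisk, and at D14 without one. The asterisk's footnote reads "outpatients visit at least every other day, or daily inpatient visit until recovery", so the recovery condition attaches to D2-13 and not to D14.

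**The concern.** In the text, one act closes three things: dosing, follow-up and SAE collection. A participant who is still taking study drug and is released by day 10 therefore leaves the required SAE window with the last dose. Take someone released on day 5 who has a serious neuropsychiatric event on day 7. The SAE clause does not require that event to be collected, although the protocol itself names this kind of risk.

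The second problem is comparability. The length of the window depends on how soon the physician stops appointments, which happens after randomization. The trial's hypotheses include less hospitalization and shorter stays on montelukast. If release also came sooner on montelukast, that arm would be observed for fewer days, and crude SAE counts by arm would not rest on equal observation time.

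Table 1 points the other way. Two hospitals could reasonably follow different rules, one closing safety collection at release and the other assessing everyone at day 14. An analysis plan cannot repair this, because it cannot recover events that were never collected.

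**Working it through.** The protocol states no figure for the post-dose safety window, so there is none to reproduce. The check is calendar arithmetic on its own stopping rules.

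**Inputs**
- R = the day the physician discontinues the follow-up appointment. The protocol gives no distribution for R, so it is varied.
- Dosing ends at the earlier of day 10 and R (Administration of allocated treatment).
- Follow-up ends at the earlier of day 14 and R (Collecting follow-up information; the 14-day cap is also in Study Design and Procedures).
- SAE collection ends with the individual's follow-up (Expected adverse events).
- Table 1 has a side-effects check at D14 with no recovery condition.
- Assumptions: day 1 is the day of randomization and first dose, as in Table 1; the last dosing day is at most day 10; the participant takes study drug until the dosing rule ends it.

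**Formulas**
- Required SAE days after the last dose, by the text: min(R, 14) − min(R, 10).
- Days from last dose to the D14 check, by Table 1: 14 − min(R, 10).

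| R (day of release) | Last dosing day | End of SAE collection, text | Days after last dose, text | Days after last dose, Table 1 |
|---|---|---|---|---|
| 3 | 3 | 3 | 3 − 3 = 0 | 14 − 3 = 11 |
| 5 | 5 | 5 | 5 − 5 = 0 | 14 − 5 = 9 |
| 7 | 7 | 7 | 7 − 7 = 0 | 14 − 7 = 7 |
| 10 | 10 | 10 | 10 − 10 = 0 | 14 − 10 = 4 |
| 11 | 10 | 11 | 11 − 10 = 1 | 4 |
| 12 | 10 | 12 | 12 − 10 = 2 | 4 |
| 13 | 10 | 13 | 13 − 10 = 3 | 4 |
| 14 or later | 10 | 14 | 14 − 10 = 4 | 4 |

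By the text, the window is 0 days for every release up to day 10 and at most 4 days after that. By Table 1, it is never below 4 days. The two rules agree only for R of 14 or later.

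**Sensitivity to day counting.** If the 10 days are counted after the immediate first dose, the last dosing day is 11. The text maximum is then 14 − 11 = 3 days, and the zero window extends to release on day 11. The contradiction is unchanged.

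**Exception.** The formula does not cover someone who stops study drug early but stays in follow-up. If drug stops on day 3 and release is on day 8, the text gives 8 − 3 = 5 days of SAE collection after the last dose.

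**The case against.** The strongest reply is that Table 1 already provides the safety check. Read as printed, its D14 entry applies to everyone, and then no participant has a zero window. This stands to the extent that a reader cannot conclude that the protocol provides no post-dose safety observation at all. It does not settle the matter, because the table speaks of side effects where the text defines a window for SAEs, and nothing says how D14 is carried out once appointments have ended.

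Other limits also stand:

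- **Early stoppers.** Collecting follow-up information keeps participants in follow-up whether or not they finish treatment. Withdrawal of consent lists neuropsychiatric symptoms as grounds for withdrawal from study treatment, and says that a participant's own wish to stop treatment is not withdrawal from follow-up. Someone taken off drug for such symptoms and still attending therefore does have post-dose observation. It would be wrong to say that only those ill beyond day 10 have any.
- **Other routes to an event.** Participants may report by telephone, staff may use medical notes, routine healthcare systems and registries, and an SAE already open is followed to resolution or stabilization. A later event might thus come to light and reach the DSMB. None of these routes extends the stated SAE window, so the accurate wording is that the event need not be collected, not that it would be lost.
- **Bias.** A reader might infer that the SAE comparison is biased in favour of montelukast by a calculable amount. The documents do not support that. They give no recovery times by arm, no SAE rate and no between-arm SAE test. The mechanism is possible, but its size is unknown.
- **Length of the window.** How long observation after the last dose should be is a separate question. The protocol gives no figure on the duration of risk from which to judge it.

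**Conclusion.** The point holds as an internal contradiction over the end of safety collection. Under the text, a participant on study drug until release by day 10 has 0 required SAE days after the last dose, and one released later has 1 to 4. Under Table 1, everyone has a side-effects check at day 14, which is 4 to 11 days after the last dose for releases from day 3 onward. The documents do not say which governs.

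The zero-day result assumes that the text overrides Table 1 and that the participant did not stop drug early. Dependence on a post-randomization event follows directly from the text. An actual difference in observation time between arms would also need treatment to change the time of release, which is not known. The matter should be corrected because SAE collection is an instruction to sites.

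**What to change.** Reconcile Duration of follow-up and Expected adverse events with Table 1 by stating the end of safety collection once. Suggested wording for Expected adverse events: SAEs and side effects are collected from screening to day 14 after randomization for every randomized participant, regardless of when clinic appointments end; those already released are contacted by telephone at day 14.

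In Duration of follow-up, add that the physician's ending of appointments does not end safety collection, and correct the closing comparison, either by supplying the missing 14-day limit or by deleting the comparison. In Table 1, label the row so that it covers SAEs as well as side effects, and note the telephone contact at D14.

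This changes data collection only; it leaves the dosing rule alone. It gives both arms the same required observation time from randomization. It does not equalize the span after the last dose, which still varies with release (9 days for release on day 5, 7 for day 7, 4 for day 10 or later) but no longer falls to zero.

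The cost is a wording amendment and one telephone contact for each participant released before day 14. A few will be unreachable and should be reported as such by arm.
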